**6.2 Description of Evaluations**

**6.2.1 Screening Evaluation**

**Consenting Procedure**

GCP guidelines will be followed for consenting procedure. A single informed consent form will describe both the screening and study procedures. The research staff at antenatal clinic will include an MD doctor and a lab technician. The doctor will conduct the consent process by explaining in English or the vernacular language (Telugu) the study procedure, purpose of the study, and choice of the participants throughout the study. The written informed consent form will be printed in the vernacular language as well as English. The participant will read the form and ask queries, which will be addressed by the doctor. The signed consent document will be maintained by the Principal Investigator.

**Screening**

The screening will be performed at the time of study entry. The history will be taken, and the participant will be assessed physically for any sign or symptom of UTI. The screening evaluation will include:

A. History Taking

a. History of recent antibiotic usage

b. History of symptoms of UTI

B. Physical Examination

a. Signs of hypovolemia

b. Temperature and blood pressure

C. Prior result of urine pregnancy test or ultrasound (for confirmation of pregnancy)

Only if the inclusion/exclusion criteria are met, will a participant be enquired about antenatal history of gravida and para, and her urine sample will be collected.

**6.2.2 Enrollment, Baseline, and/or Randomization**

**Enrollment**

After screening, the enrolled participants will be enquired about more history and the urine sample will be collected. The randomization sequence will be concealed from the enrolling doctor. The randomization will be done in microbiology laboratory by the Principal Investigator. The date of enrollment will be the date of first antenatal visit, when in the same visit, her urine sample is collected, history is taken, and she is randomized to one of the arms.

**Baseline Assessments**

1. History taking

2. Physical examination

3. Rapid test on urine sample in case of intervention arm

**Randomization**

Randomization will be done on the same day of screening, baseline, and urine sample collection. Randomization will be done as soon as the sample reaches microbiology laboratory. The allocation sequence like the one generated by MS excel random number generation feature will be concealed from the research staff who will enroll the participants.

**6.2.3 Blinding**

Blinding will be done for outcome assessors, who will be provided only identification details of the enrolled participants. Under no circumstance, will the blinding be broken. The outcome assessors will at least be graduates with some experience in field epidemiology.

**6.2.4 Followup Visits**

Although study will not require any additional follow up visit to the hospital, but the participants will be encouraged to come for regular antenatal checkups as scheduled by the obstetricians. The routine tests and assessment of antenatal checkups will be carried out as per the guidelines of the institute. In case of any adverse event or urinary tract infection, the participants will be shared contact number of the Principal Investigator and research staff, who will facilitate the care provision at the hospital.

Since the participants need not deliver in Gandhi Hospital itself, or may not necessarily deliver around the Expected Date of Delivery, a follow up visit will be conducted by outcome assessors to the hospital where they will be admit or at home if the delivery is already over. The coordination will be done around EDD on telephone.

The follow up visit should be completed by the outcome assessors around the delivery or as soon as possible. The outcome assessors will collect data on week of gestation at the time of delivery, birth weight, any maternal or perinatal co-morbidity encountered, and will collect the snapshot of the discharge card or treatment record as per the availability with the participant.

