**3. STUDY DESIGN**

The study will be a parallel-group superiority pragmatic randomized controlled trial with 1:1 allocation, to identify the superiority of the intervention of using a rapid test for informing clinical decision for prescribing antibiotics based on positive AST results, over the usual care in the study hospital in case of asymptomatic bacteriuria in pregnancy. Blinding will be done for outcome assessors.

The only difference between the intervention and control arm will be the information provided by the rapid test regarding the identification of bacteria and susceptibility of antibiotics.

The primary outcome of the study is incidence of preterm birth or low birth weight or both as the outcome of pregnancy. The secondary outcome is incidence of any other maternal or perinatal complication in the study participants.

The study population will be pregnant women attending antenatal clinic of the hospital for first antenatal check-up. The study will have two arms- intervention arm and control arm. In each arm, 120 participants will be enrolled.

The setting of conduct of study will be antenatal outpatient clinic and microbiology laboratory of Gandhi Medical College and Hospital, Secunderabad. The reader machine for the novel test will be installed in the microbiology laboratory of Gandhi Hospital by Department of Biological Sciences, Birla Institute of Technology and Science (BITS) Pilani, Hyderabad Campus. The strips for conducting the test will be provided by Genomics Laboratory, Department of Biological Sciences, BITS Pilani, Hyderabad Campus.

Anticipated duration of study is one year, including a variable follow up period depending upon the Expected Date of Delivery of pregnant women.

Unit of randomization will be pregnant woman. A suitable method of randomization will be adopted out of coin toss, lottery, toss of dice, shuffling cards, MS Excel etc. The randomization sequence will be concealed from the staff enrolling and assessing. Simple randomization method will be adopted to randomly assign participants to either intervention or control group without any restriction. The Principal Investigator will discard urine samples of participants of control arm and will provide urine sample of participants of intervention arm to the staff in laboratory conducting rapid test, as per the randomization sequence. The positive samples will be informed to obstetrician on duty and will be prescribed antibiotics as per the report of the rapid test.

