**5.4 Adherence Assessment**

A telephonic follow-up will be done with those participants who will be prescribed antibiotics, so as to ensure and assess adherence till they take all the pills as per the prescribed regimen. The adherence will be assessed based on the information shared by the participants about the remaining pills.

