**6. STUDY PROCEDURES**

**6.1 Schedule of Evaluations**

| **Assessment** | **Screening, baseline enrollment, randomization: Visit-1** | **Telephonic Follow up 1 (Day 1)** | **Telephonic Follow up 2 (Day 3)** | **Telephonic Follow up 3 (Day 7)** | **Physical Follow up Visit (EDD around 9 months of pregnancy)** |
| --- | --- | --- | --- | --- | --- |
| Informed Consent Form | **X** |  |  |  |  |
| Demographics | **X** |  |  |  |  |
| Medical History | **X** |  |  |  |  |
| General Physical Examination | **X** |  |  |  |  |
| Current Medications | **X** |  |  |  |  |
| Blood Chemistries (As per antenatal checkup) | **X** |  |  |  |  |
| Hematology (As per antenatal checkup) | **X** |  |  |  |  |
| Vital Signs (As per antenatal checkup) | **X** |  |  |  |  |
| Inclusion/Exclusion Criteria | **X** |  |  |  |  |
| Enrollment/Randomization | **X** |  |  |  |  |
| Rapid Test | **X** |  |  |  |  |
| Treatment Administration | **X** |  |  |  |  |
| Telephonic follow-up |  | **X** | **X** | **X** |  |
| Adverse Events |  | **X** | **X** | **X** |  |
| Outcome Assessment |  |  |  |  | **X** |

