**7.5 Followup for Adverse Events**

The participant experiencing adverse event will be followed up throughout the remaining pregnancy once a week for any residual morbidity.

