**9.2 Sample Size and Randomization**

Sample size was calculated based on type 1 error of 5%, power of 80%, global rate of preterm birth as 10.6% and that of low-birth-weight as 14.6%, combined rate of preterm or low-birth-weight (primary outcome measure) extrapolated as 25%. Based on the contribution of asymptomatic bacteriuria to total preterm birth and low-birth-weight, which varies from 6.9% to 20.5%24, the expected incidence of preterm birth or low-birth-weight in intervention arm for sample size calculation, was safely assumed to be 15% lower than the above-extrapolated global incidence of 25% in the control arm, as a minimally important difference for success of the experiment. Loss to follow up was accounted for 10% participants (5% in each arm). The sample size calculation estimated 120 participants to be enrolled in each arm, with a total 240 participants to be enrolled in the study.

Intention-to-treat analysis will be done in the original groups in which the participants are allocated. Incidence of other maternal and perinatal events will be described as frequencies. In case there is loss to follow up, complete case analysis will be done. In case there is any protocol deviation, per protocol analysis will be done.

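### The only outcome contact is timed to the expected date of delivery, so every preterm birth is first sought weeks after it has happened

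*Protocol*

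**What the plan says.** Protocol section 3 defines the endpoint: "The primary outcome of the study is incidence of preterm birth or low birth weight or both as the outcome of pregnancy". Section 9.5.1 has it measured at the visit after delivery.

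Two places set the timing of that visit. In the schedule (6.1), outcome assessment appears in one column only, headed "Physical Follow up Visit (EDD around 9 months of pregnancy". In 6.2.4 the arrangement is: "The coordination will be done around EDD on telephone".

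Section 6.2.4 also recognises that women "may not necessarily deliver around the Expected Date of Delivery, a follow up visit will be conducted by outcome assessors", either at the admitting hospital or at home if the birth is over. It states the aim: "The follow up visit should be completed by the outcome assessors around the delivery or as soon as possible".

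The other contacts are narrower. Section 5.4 says: "A telephonic follow-up will be done with those participants who will be prescribed antibiotics"; the schedule puts these calls on days 1, 3 and 7. Section 7.5 says: "The participant experiencing adverse event will be followed up throughout the remaining pregnancy once a week for any residual morbidity". Sections 6.2.4 and 7.2 have women ring the team about adverse events, side effects or urinary infection. None of these asks a woman to report that she has delivered.

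On missing outcomes, section 9.2 says: "In case there is loss to follow up, complete case analysis will be done".

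**The concern.** A term birth falls close to the planned contact; a preterm birth, by definition, does not. The women who have this component of the endpoint are therefore the ones contacted longest after the event. They may have delivered at any hospital, and 6.2.4 relies on whatever discharge card or treatment record the woman still has.

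At stake is the completeness and reliability of the primary outcome. If contact or records are lost more often after a preterm birth, the missing cases are mostly events, and a complete-case analysis removes them. The overall loss could still look close to what was planned, because preterm births are a small share of all births.

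**Working it through.** **1. Is there an earlier trigger?** Setting the sections side by side:
- Sections 6.1 and 6.2.4: telephone coordination and visit around the expected date.
- Section 5.4 and the schedule: calls on days 1, 3 and 7, described only for women prescribed antibiotics.
- Section 7.5: weekly contact, only after an adverse event.
- Sections 6.2.4 and 7.2: the woman rings, about adverse events, side effects or urinary infection.

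For participants in general, no study contact is scheduled between the enrolment period and the expected date. The stated aim of a prompt visit has no stated means behind it when the birth is early.

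**2. Length of the delay.** Assumptions, since the protocol defines neither: preterm means before 37 completed weeks, and the expected date is at 40 weeks. Delay = 40 − gestation at delivery.

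| Gestation at delivery | Weeks before the expected date |
|---|---|
| 36 weeks 6 days | 3.1 |
| 36 weeks | 4 |
| 34 weeks | 6 |
| 32 weeks | 8 |
| 28 weeks | 12 |

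A call one or two weeks before the expected date would shorten each gap but would still follow every preterm birth.

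**3. The planned comparison.** Inputs from 9.2: control rate 25%, preterm rate 10.6%, type 1 error 5%, power 80%, 5% loss in each arm. Reading the 15% reduction as absolute gives 25% against 10%. A two-sided test with continuity correction needs 113 per arm, and 113 / 0.95 = 118.9, so 119, which agrees with the stated 120.

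**4. Effect of loss concentrated in preterm births.** Assumptions not in the protocol: preterm cases are the same share of events in both arms, 10.6 / 25 = 42.4%, and the loss rates are illustrative and equal by arm.

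Observed rate = [preterm × (1 − loss after preterm) + other events × (1 − other loss)] / [preterm × (1 − loss after preterm) + (1 − preterm) × (1 − other loss)].

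With 20% loss after preterm birth and 5% otherwise:
- Control: (0.106 × 0.80 + 0.144 × 0.95) / (0.106 × 0.80 + 0.894 × 0.95) = 0.2216 / 0.9341 = 23.7%.
- Intervention: (0.0424 × 0.80 + 0.0576 × 0.95) / (0.0424 × 0.80 + 0.9576 × 0.95) = 0.0886 / 0.9436 = 9.4%.

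With 40% and 5%:
- Control: 0.2004 / 0.9129 = 22.0%.
- Intervention: 0.0802 / 0.9352 = 8.6%.

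| Loss after preterm / otherwise | Rates | Risk difference (points) | Risk ratio | Odds ratio | Power, 120 enrolled per arm |
|---|---|---|---|---|---|
| 5% / 5% | 25.0% v 10.0% | 15.0 | 0.400 | 0.333 | 85.1% |
| 20% / 5% | 23.7% v 9.4% | 14.3 | 0.396 | 0.333 | about 83% |
| 40% / 5% | 22.0% v 8.6% | 13.4 | 0.390 | 0.333 | 79.6% |

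Power here is without continuity correction, which is why it starts above the planned 80%.

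**5. Number of women affected.** At 10.6% in both arms, 0.106 × 240 = 25.4 preterm births. Under the hypothesised effect, 120 × 0.106 + 120 × 0.0424 = 12.7 + 5.1, about 18.

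**The case against.** Late contact is not loss. Date of delivery and birth weight are fixed at birth. The assessor form (Appendix 4) takes the delivery date and lists the documents to photograph, and the enrolment form (Appendix 3) holds gestational age, so preterm status can be worked out weeks later. Section 9.5 has outcomes validated against medical records, and 10.3.5 has 5% of delivered women revisited. Section 6.2.4 foresees early delivery, and its reference to the expected date carries no fixed window. All of this stands, and it limits the harm.

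Three stronger readings are tempting, and the protocol supports none of them:
- **A prompt visit after a preterm birth is impossible.** A woman might ring unprompted, since she has the team's number. What the text shows is that no earlier trigger is stated.
- **Records and contact will be lost more often after a preterm birth.** Only the delay follows from the document. Greater loss is a plausible risk, but hospital care of a preterm baby might equally leave more paperwork.
- **The treatment comparison is seriously distorted.** With loss similar by arm, the table shows little movement in the risk difference, almost none in the risk ratio and none in the odds ratio. The chi-square test of 9.6 remains valid under the null.

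The objection does not supply a way of learning of an early delivery. The home visit says where the assessor goes, not when the team finds out.

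**Conclusion.** The point holds as a flaw in measurement timing with modest statistical consequences. The stated trigger works against the stated aim of 6.2.4 for one component of the primary endpoint: a contact made at the expected date follows every preterm birth by more than 3 weeks, on the 37- and 40-week conventions.

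The consequence is conditional. If loss is greater after preterm birth and similar by arm, incidence is understated, the risk difference shrinks somewhat and some power is lost: about 2 percentage points of power at an assumed 20% loss after preterm birth, and between 5 and 6 at 40%, against uniform 5% loss. Only the 40% case takes power just below 80%. These loss rates are assumptions; the protocol gives no information on loss by outcome. A change is justified because the gap falls on the endpoint itself and is cheap to close.

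**What to change.** Change 6.2.4 and the 6.1 schedule as follows:
- At enrolment, ask every woman in both arms to ring the study number when she delivers, wherever that is.
- Add brief calls before 37 weeks on the same schedule in both arms, for example at 32 and 36 weeks. Time them from gestational age at enrolment: women may enrol in any trimester, so some will need one call or none.
- Have the calls made by staff other than the blinded assessors, or in a way that does not reveal allocation, because assessors are meant to receive identification details only.
- Count the outcome-visit window from the reported delivery, and state its length.
- Keep the call around the expected date as a backstop. It remains necessary, because a birth after the last early call is still missed if the woman does not ring.

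Cost: at most about 2 × 240 = 480 short calls by existing staff, one added instruction at enrolment and an edited schedule table. No extra visit or procedure is needed.

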**6.2.5 Completion/Final Evaluation**

Any adverse event will be reported telephonically by the participant during telephonic follow-up. In case of symptomatic UTI, rapid test will be conducted for the participant again and antibiotic regimen will again be prescribed. No other evaluation is needed for repeat visit of the participant.

**7. SAFETY ASSESSMENTS**

In case any adverse event due to antibiotic is experienced, the antibiotic will be discontinued. In case UTI is experienced by participants of intervention as well as control arm, the participant will undergo repeat testing and will be given antibiotics, so as to progress the infection to pyelonephritis.

**7.1 Specification of Safety Parameters**

For symptomatic UTI experienced later in the course of pregnancy, temperature more than 99 F will be considered as fever. The result of rapid test will be regarded as final, although the obstetrician will be free to order a urine culture to confirm the report.

**7.2 Methods and Timing for Assessing, Recording, and Analyzing Safety Parameters**

At any time during the pregnancy after the enrollment in the study, if a participant experiences any side effect of antibiotics or signs and symptoms of UTI, the participant will call the Principal Investigator or research staff. The risk of encountering UTI is higher in second and third trimester [35].

**7.3 Adverse Events and Serious Adverse Events**

Although the study involves urine collection and prescription of commonly prescribed antibiotics which have been safely used since last many years, in case any participant experiences any adverse event due to consumption of antibiotics, the participant will be promptly transported to the hospital and managed accordingly. The adverse events and serious adverse events will be reported to the regulatory authorities and ethics committee, as well as to the sponsor immediately. The detailed reports will be submitted as per GCP guidelines.

In case the participant does not respond to an antibiotic labelled as susceptible by the rapid test, a confirmatory urine culture will be conducted on day three after the prescription.

**7.4** **Reporting Procedures**

Principal Investigator will be responsible to report any adverse event immediately to the sponsor and ethics committee. In case an adverse event occurs due to an antibiotic, the same will not be prescribed again to the participant. Since the antibiotics used by the obstetricians will be routinely used in clinical practice, the remaining participants will still be prescribed the antibiotics as per the report of the rapid test.

**7.5 Followup for Adverse Events**

The participant experiencing adverse event will be followed up throughout the remaining pregnancy once a week for any residual morbidity.

**7.6 Safety Monitoring**

The sponsor will conduct periodic monitoring visits to the trial site and BITS Pilani laboratory. Regular update of the trial progress will be shared with the funder in review meetings (frequency will be decided by the funder).

**8. INTERVENTION DISCONTINUATION**

The criteria for discontinuing the intervention for a participant:

1. If the participant experiences any adverse event due to an antibiotic prescribed, the participant can discontinue the regimen prescribed and seek medical help.

2. If the participant decides to no more be a part of the study and refuses to provide the information related to the outcome of pregnancy

The criteria for discontinuation of the intervention of rapid test:

1. If more than 10% participants report that the antibiotics prescribed based on the results of the rapid test could not arrest the disease process or turn symptomatic (although the rapid test has been validated in multicentric studies previously)

Even if the participants discontinue antibiotic regimen, they will be followed up for the outcomes of the pregnancy. Participants need to report any signs and symptoms of UTI if they discontinue the antibiotic regimen.

**9. STATISTICAL CONSIDERATIONS**

**9.1 General Design Issues**

The process of development of prematurity and low birth weight due to asymptomatic bacteriuria is largely insidious and multifactorial. Training status of lab technicians, resource availability, adherence to guidelines, myths among the providers regarding asymptomatic nature of the disease and lack of habit of conducting point-of-care tests in routine antenatal check-ups introduce variability at facility level. Hence, to study the effect of early diagnosis of asymptomatic bacteriuria and subsequent targeted therapy in real-world situation, pragmatic randomized controlled trial design was chosen. The primary hypothesis is that early diagnosis and treatment of asymptomatic bacteriuria will decrease preterm and low birth weight. The primary outcome measure is incidence of preterm and/or low birth weight in usual care of a setting and in an intervention arm with early diagnosis using rapid test and subsequent informed treatment with antibiotics. Hence parallel study design was chosen to prove the superiority of the intervention. Secondary hypothesis was that some co-morbidities can be confounders for preterm and low birth weight which are otherwise multifactorial. Hence, secondary outcome measure was the incidence of maternal and perinatal co-morbidities.

**9.2 Sample Size and Randomization**

Sample size was calculated based on type 1 error of 5%, power of 80%, global rate of preterm birth as 10.6% and that of low-birth-weight as 14.6%, combined rate of preterm or low-birth-weight (primary outcome measure) extrapolated as 25%. Based on the contribution of asymptomatic bacteriuria to total preterm birth and low-birth-weight, which varies from 6.9% to 20.5%24, the expected incidence of preterm birth or low-birth-weight in intervention arm for sample size calculation, was safely assumed to be 15% lower than the above-extrapolated global incidence of 25% in the control arm, as a minimally important difference for success of the experiment. Loss to follow up was accounted for 10% participants (5% in each arm). The sample size calculation estimated 120 participants to be enrolled in each arm, with a total 240 participants to be enrolled in the study.

Intention-to-treat analysis will be done in the original groups in which the participants are allocated. Incidence of other maternal and perinatal events will be described as frequencies. In case there is loss to follow up, complete case analysis will be done. In case there is any protocol deviation, per protocol analysis will be done.

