**Sample Size and Population**

Sample size proposed for the study is 120 pregnant women in each of the intervention and control arm.

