**Prevalence**

Prevalence of asymptomatic bacteriuria in pregnant women is reported to be 1.9 to 9.5% [1, 9], while that of any form of Urinary tract infections in pregnant women is 2 to 10% [10]. Thus 90 to 95% of UTI in pregnant women is asymptomatic.

The various risk factors for increased prevalence of UTI or asymptomatic bacteriuria being- low socio-economic status, advanced maternal age, multi-parity, increasing period of gestation, poor sanitation, lack of general hygiene and failure to attend antenatal clinic [11-13].

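### Section 9.2 argues for the effect as a relative share of births, but 120 per arm follows only from a 15-percentage-point drop; power for the argued effect is about 5–16%, not 80%

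*Protocol*

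**What the plan says.** Section 9.2 gives the design inputs. On error rates: "Sample size was calculated based on type 1 error of 5%, power of 80" (per cent). On the control arm: "combined rate of preterm or low-birth-weight (primary outcome measure) extrapolated as 25" (per cent). The effect is introduced by "Based on the contribution of asymptomatic bacteriuria to total preterm birth and low-birth-weight, which varies from 6.9% to 20.5" (per cent), and the intervention-arm incidence then "was safely assumed to be 15% lower than the above-extrapolated global incidence of 25% in the control arm". The same sentence presents this gap as the minimally important difference. On attrition: "Loss to follow up was accounted for 10% participants (5% in each arm"). The result is 120 per arm, 240 in all.

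Section 9.2 does not say whether the 15% is relative or in percentage points. It also says that complete cases will be analysed if women are lost. Section 9.6 names Pearson's chi-square on the 2x2 table of arm by outcome. Section 2.1, under Prevalence, states: "Prevalence of asymptomatic bacteriuria in pregnant women is reported to be 1.9 to 9.5" (per cent); under Screening the same section puts it as high as 10%. Under Section 3, unselected women at a first antenatal visit are randomised, and in the intervention arm those with a positive rapid test are prescribed antibiotics.

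**The concern.** The justification and the calculation appear to use different scales. The contribution of a cause to the total number of events is a fraction of those events. It limits how far the incidence can fall in relative terms if that cause is removed. A figure of 15% lies inside the cited 6.9–20.5% range only when read as relative. Read as percentage points, it removes 60% of all events, about three times the top of the cited range (60/20.5 = 2.9).

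This input decides whether the trial can answer its primary question. If the sample size rests on the larger effect while the argument supports only the smaller one, a reader of 9.2 will believe that the trial has an 80% chance of detecting the argued benefit when the chance is far lower. A non-significant result would then carry little information about that benefit, and nothing in the protocol would warn the reader.

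**Working it through.** **Inputs.** Two-sided 5% (9.2 does not state sidedness; two-sided matches a Pearson chi-square), power 80%, control rate p1 = 0.25, 1:1 allocation (Section 3), 5% loss per arm (9.2), so 120 × 0.95 = 114 evaluable per arm.

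**Formulas.** With d = p1 − p2 and p̄ the mean of p1 and p2:

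- n = [1.96·√(2p̄(1−p̄)) + 0.8416·√(p1(1−p1)+p2(1−p2))]² / d²
- Continuity-corrected n′ = (n/4)·[1 + √(1 + 4/(n·d))]²
- Power = Φ{[d − 1.96·√(2p̄(1−p̄)/n)] / √[(p1(1−p1)+p2(1−p2))/n]}

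**Step 1: reproduce 120.** For 25% vs 10%:

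- n = [1.96·√0.28875 + 0.8416·√0.2775]² / 0.15² = 99.5, so 100.
- n′ = (99.5/4)·[1 + √(1 + 4/(99.5·0.15))]² = 112.5, so 113.
- 113/0.95 = 118.9, so 119, which is the plan's 120 after rounding.

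Other two-sided routes for 25% vs 10% do not land there: without correction, 106 (5% loss) or 112 (10% loss); with correction and 10% loss, 126. One-sided routes give at most 103.

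**Step 2: the relative reading.** 0.25 × (1 − 0.15) = 0.2125. Then n = [1.96·√0.35555 + 0.8416·√0.35484]² / 0.0375² = 1,983.3, so 1,984 evaluable per arm (2,089 with 5% loss). This cannot be the origin of 120.

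**Step 3: the effect that the cited share supports.** If every attributable event were removed, the drop is 0.25 × 0.069 = 1.7 points (to 23.3%) up to 0.25 × 0.205 = 5.1 points (to 19.9%).

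**Step 4: power with 114 and 120 evaluable per arm.** The exact column enumerates the uncorrected Pearson chi-square and counts both tails.

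| Comparison | Formula, 114 / 120 | Exact, 114 / 120 |
|---|---|---|
| 25% vs 23.3% (6.9% relative) | 4.9% / 5.0% | 6.1% / 6.2% |
| 25% vs 21.25% (15% relative) | 9.9% / 10.2% | 10.3% / 10.6% |
| 25% vs 19.9% (20.5% relative) | 15.1% / 15.6% | 15.3% / 15.9% |
| 25% vs 10% (15 points) | 85.1% / 86.9% | 86.1% / 88.0% |

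By the formula, 80% power is reached at a drop of 14.2 points (114 per arm) or 13.9 points (120 per arm).

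**Step 5: plausibility against the cited prevalence.** Only women who test positive can benefit. Suppose that the test finds all bacteriuric women and only those, that each would otherwise have the outcome, and that treatment always prevents it. The drop across all randomised women then equals the prevalence. At 9.5 points (25% vs 15.5%) power is 43–45%; at 10 points (25% vs 15%) it is 47–50%. Both drops are short of 15 points.

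**Step 6: precision.** The 95% half-width for the risk difference at 25% vs 21.25% is 1.96·√[(0.25·0.75 + 0.2125·0.7875)/114] = 10.9 points, about twice the largest drop in step 3.

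**The case against.** The strongest reply is that the calculation is sound on its own terms. The figure of 120 reproduces, and for 25% vs 10% the planned test does better than 80%. That stands: this is not a computing slip, and the 80% is true for a 15-point drop. What fails is the link between that drop and its stated support. The scale is unlabelled, and the absolute reading is inferred because only it gives 120. If the 6.9–20.5% were itself in percentage points, power would run from about 25% to over 99%, but a contribution to a total does not read that way. The source of the range is not available, so this rests on the protocol's wording.

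Two stronger readings are tempting and not supported. A reader might infer that a 15-point drop is impossible because at most 9.5% of women are bacteriuric. The protocol reports a literature range, not a bound for this hospital. It mentions 10% elsewhere, lists low socio-economic status and later gestation as raising prevalence, and enrols largely such women in any trimester. It also gives no false-positive rate, so the share treated is unknown. Implausible is the right word. A reader might also infer that a null result is all but certain even if screening works. The figures give non-significance in about 84–95% of trials over the cited range, and in about half or slightly more at the step 5 ceiling. Nor does the protocol say that a null would be taken as failure of screening; it simply does not guard against that.

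Finally, the figures depend on the 25% control rate, which is close to the sum of two overlapping rates (10.6% + 14.6% = 25.2%). Assuming 30–40% instead, power for a 15% relative reduction is 12–16%, so the conclusion holds although the exact values move.

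**Conclusion.** The point holds. Section 9.2 supports its effect with a relative fraction and sizes the trial on an absolute difference four times as large as the same 15% taken relatively (15 against 3.75 points). At a 25% control rate, two-sided 5% and 114–120 evaluable per arm, the trial has 80% power only for a drop of about 14 points or more. It has about 10–11% power for a 15% relative reduction and about 5–16% over the cited 6.9–20.5%. The assumed 15 points is also implausible, though not ruled out, on the cited prevalence. The conclusion rests on reading the cited contribution as a share of events, which is what the wording says. Calling the assumption safe and the difference minimally important is not justified by the support given. This should be corrected, because it concerns the power claim for the primary outcome.

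**What to change.** No extra women and no change to care are needed.

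- **Section 9.2:** say whether the 15% is relative or in percentage points. State that, at a 25% control rate, 120 per arm gives 80% power for a drop of about 14 points, about 10–11% for a 15% relative reduction, and about 5–16% over 6.9–20.5%. Remove the descriptions of the assumption as safe and of the difference as minimally important.
- **Section 9.6:** add the risk difference with its 95% confidence interval (expected half-width about 11 points), and state that a non-significant result will not be read as absence of effect.
- **Sections 3 and 9.1:** bring the wording about showing or proving superiority into line with what the sample can detect.

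The Précis gives only the number per arm and no power, so its sample-size line can stand. Relabelling the trial as a pilot is not required. If the sponsor wants 80% power for a 15% relative reduction, the alternative is about 1,984 evaluable women per arm. The cost of the wording change is that the stated power becomes much less favourable.
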